### 2.3. Sample Size Justification

Using G*Power 3.1.9.7. (Heinrich-Heine-Universität Düsseldorf, Düsseldorf, Germany), we powered a repeated-measures ANOVA (within subjects, 4 timepoints). With effect size f = 0.25 (≈Cohen’s d = 0.5, moderate), α = 0.05, power = 0.80, and correlation among repeated measures r = 0.50, the minimum required sample is N = 159. Allowing for 15% attrition, we plan to recruit N = 180 (≈60 per diagnostic group), ensuring adequate precision for primary and secondary analyses.

The selected sample size (N = 180) ensures adequate precision for detecting moderate within-subject effects (Cohen’s d ≈ 0.5) across four timepoints, representing a balance between feasibility and statistical power. This sample is consistent with or larger than comparable nurse-led self-care intervention studies in chronic patients (typically N = 100–150) [19,20,21]. Given the multicenter design and inclusion of three major chronic conditions (COPD, diabetes, and CVD), the findings will allow reasonable generalization to similar community and primary-care populations within Southern Italy and comparable European settings.

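### The stated inputs for the within-subject repeated-measures ANOVA do not give N = 159; they give about 24, so the sample-size justification must be restated (the error runs toward excess power)

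*Protocol article*

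**What the plan says.** Section 2.3 names the software ("Using G*Power 3.1.9.7"), the test ("we powered a repeated-measures ANOVA (within subjects, 4 timepoints") and the inputs: "With effect size f = 0.25 (≈Cohen’s d = 0.5, moderate), α = 0.05, power = 0.80", with "correlation among repeated measures r = 0.50". From these it concludes that "the minimum required sample is N = 159". It continues: "Allowing for 15% attrition, we plan to recruit N = 180 (≈60 per diagnostic group", and presents this as precise enough for the primary and the secondary analyses alike. The next paragraph repeats that the sample "ensures adequate precision for detecting moderate within-subject effects (Cohen’s d ≈ 0.5) across four timepoints".

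Section 2.8 makes the within-subject repeated-measures ANOVA on the SC-CII total and domains the primary analysis, followed by Bonferroni-adjusted timepoint contrasts if the omnibus test is significant. Diagnosis enters only through subgroup analyses and as a regression predictor. The Strengths and Limitations section confirms that there is no control group. Sections 2.6 and 2.7 treat a rise of at least 8 points in the SC-CII total as clinically important.

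**The concern.** The section gives the test, almost all its inputs and the result, so the result can be checked. A requirement of 159 is implausibly large for a four-timepoint within-subject test at a moderate effect with correlation 0.50, because each patient serves as their own control and contributes four measurements.

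If 159 belongs to another test, then neither that minimum nor the power of 0.80 describes the primary analysis. A reader would take the study to be just large enough for a moderate effect, when it can detect much smaller ones. A significant omnibus test would then say little about whether the change is large enough to matter. The general statement about precision would also rest on a calculation that covers neither the primary contrast nor the comparisons between diagnoses.

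**Working it through.** **Inputs (section 2.3):** m = 4 timepoints, f = 0.25, alpha = 0.05, target power 0.80, r = 0.50, stated N = 159, attrition 15%, recruitment 180. Epsilon and the effect-size convention are not stated. A single common correlation implies compound symmetry, hence epsilon = 1; lower values are tried below.

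**Step 1: try to reproduce 159.** For the within-subject F test with one cohort, λ = f²·N·m·ε/(1 − r), df1 = (m − 1)ε, df2 = (N − 1)(m − 1)ε.

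- N = 24, ε = 1: λ = 0.0625 × 24 × 4 / 0.5 = 12.0, df = 3 and 69, power 0.817.
- N = 23, ε = 1: λ = 11.5, power 0.797.

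The requirement is therefore 24, not 159. With three groups it is still 24 (power 0.815).

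**Step 2: vary what is not stated, then the inputs themselves.**

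| Variant | N for power 0.80 |
|---|---|
| ε = 0.75 / 0.5 / 1/3 (lower bound) | 29 / 38 / 50 |
| Two other effect-size conventions, λ = f²·N·(m − 1) and λ = f²·(N − 1)·(m − 1) | 60 / 61 |
| Multivariate (MANOVA) approach | 26 |
| r = 0 in place of 0.50 | 45 |
| r = 0 and ε = 1/3 together | 97 |
| Time-by-group interaction, 3 groups | 30 |
| Between-group factor of a repeated-measures design, 3 groups | 102 |
| Non-standard λ = f²·N | 176 |

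None gives 159.

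**Step 3: look for a test that does give 159.** One-way between-subjects ANOVA, 3 groups, λ = f²·N, df = 2 and N − 3:

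- N = 159 (53 per group): λ = 9.94, power 0.805.
- N = 156 (52 per group): λ = 9.75, power 0.797.

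With equal groups the requirement is exactly 159. This test uses neither the four timepoints nor r = 0.50.

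**Step 4: what the planned sample delivers.** 180 × 0.85 = 153 completers, or 51 per diagnosis if evenly split.

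- *Omnibus within-subject test at f = 0.25:* for N = 153 and ε = 1, λ = 0.0625 × 153 × 4 / 0.5 = 76.5 and power is above 0.9999. At ε = 1/3, λ = 25.5 and power is 0.9989. At N = 159 and ε = 1/3, power is 0.9992.
- *Detectable f at 80% power, N = 153:* 0.095 at ε = 1; 0.140 at ε = 1/3.
- *Paired T0 to T3 change, two-sided, N = 153:* 0.228 SD of change at alpha 0.05 (noncentrality 0.228 × √153 = 2.82). At alpha 0.05/6, assuming all six pairwise contrasts are tested, 0.285 SD. Power at 0.228 SD with that adjustment is only about 0.56.
- *Difference in change between two diagnoses, 51 per group, alpha 0.05 unadjusted:* 0.56 SD (noncentrality 0.56 × √(51/2) = 2.83).

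**Step 5: in SC-CII points.** The article gives no SD of change. With assumed SDs of 15 and 20:

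- paired, unadjusted: 0.228 × 15 = 3.4 and 0.228 × 20 = 4.6 points;
- paired, adjusted for six contrasts: 0.285 × 15 = 4.3 and 0.285 × 20 = 5.7 points;
- between two diagnoses: 0.56 × 15 = 8.4 and 0.56 × 20 = 11.2 points.

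**The case against.** The strongest reply is that the error is in the safe direction. No endpoint, test or recruitment target changes, and the primary test has ample power. That stands: the justification is wrong, but the size of the study does not fail. Nor does the plan rest on significance alone, since section 2.8 already reports mean differences with 95% confidence intervals and effect sizes.

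It can also be said that N = 24 depends on an epsilon and an effect-size convention that the article does not state. This is true, but the ordinary alternatives for the within-subject test with the stated inputs reach 61 at most, so the failure to reproduce 159 does not hinge on them.

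Four stronger readings are tempting and are not supported:

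- *That 159 certainly comes from a three-group one-way ANOVA.* The match is exact, and a target of about 60 per diagnosis fits it, but the article names no such test. It remains an inference.
- *That the study is inadequate for comparing diagnoses.* At f = 0.25 the three-group interaction needs 30 patients, and a one-way three-group comparison at 153 has power 0.79. A shortfall against 8 points appears only with a pairwise test of change scores and SDs that the article does not give.
- *That equating f = 0.25 with d = 0.5 is an error in its own right.* It is the conventional f = d/2 label. The implied f depends on the time profile: a T0 to T3 change of 0.5 SD gives 0.186 if the rise is equal at each step, 0.217 for a step straight after baseline, and 0.25 if two timepoints sit at each extreme. The article specifies no profile.
- *That 153 completers, being fewer than 159, leave the primary test short.* Since 159 is not its requirement, no loss of power follows.

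**Conclusion.** The point holds as an arithmetic error in the justification. The stated test and inputs give N = 24 at epsilon = 1 and 50 at the lower-bound epsilon, against a stated 159, which is 6.6 and 3.2 times as many. The power of 0.80 attached to f = 0.25 is likewise not that of the primary analysis; at 153 to 159 completers it is above 0.99 across the whole range of epsilon, taking r = 0.50 as stated.

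The consequence is one of interpretation: the omnibus test can detect effects far smaller than the moderate one the section describes. The detectable changes in SD units rest on 153 completers, 51 per diagnosis, and, for the adjusted figure, an assumed six contrasts. Any figure in points rests in addition on an assumed SD of change.

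**What to change.** Reword section 2.3 as follows.

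1. Delete 159 as the requirement for the within-subject test. Keep 180 recruits, giving 153 completers after 15% attrition, and justify that number by precision.
2. State what 153 completers deliver at 80% power: f of about 0.095 for the omnibus test (at epsilon = 1), and for the paired T0 to T3 change about 0.23 SD of change unadjusted, or about 0.285 SD with Bonferroni adjustment over six contrasts. Say how many contrasts are intended, so that the adjusted figure matches section 2.8.
3. Convert to SC-CII points only with an SD of change that is stated and labelled as an assumption.
4. Replace the general claim of precision for primary and secondary analyses with the detectable pairwise difference in change between diagnoses: about 0.56 SD at 51 per group, unadjusted.
5. Say that the 95% confidence interval already planned for the mean change will be read against the 8-point threshold.

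The cost is a rewritten paragraph, with no extra patients or data. Sections 2.11 and 2.13 describe ethics approval as pending and registration as still to come, so the correction can be made before either is final.

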### 2.14. Study Flow and Timeline

Table 2 summarizes participant progression, intervention schedule, and data-collection timepoints. Eligible patients with COPD, T2DM, or CVD will be screened by Family and Community Nurses and enrolled after digital informed consent. Four assessments occur at baseline (T0), 3 months (T1), 6 months (T2), and 12 months (T3). Each assessment includes completion of the SC-CII and disease-specific self-care scales (SCHFI/SCODI/SCCOPD), HRQoL measures (EQ-5D-5L, SF-36), and the MSPSS.

The 12-month nurse-led digital educational intervention consists of four individualized tele-education sessions (T0–T3) and asynchronous follow-up materials between sessions. Data are stored in encrypted servers and monitored monthly for quality assurance.

Recruitment will be conducted over approximately nine months across all participating centers until the planned sample size (N = 180) is reached. Enrollment will close upon completion of the recruitment window or attainment of the target sample, whichever occurs first. To address potential loss to follow-up, participants will receive automated reminders and flexible scheduling options for each tele-education session and assessment. Follow-up completeness will be reviewed monthly, and participants lost to contact will be reached by telephone and email (up to three attempts) before being considered dropouts.

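### Section 2.3: recruiting 180 with 15% attrition leaves 153 completers, 6 below the plan's own minimum of 159. This is a minor arithmetic error that does not threaten the primary test.

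*Protocol article*

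**What the plan says.** Section 2.3 of the protocol article describes the calculation as "we powered a repeated-measures ANOVA (within subjects, 4 timepoints". Its inputs are "With effect size f = 0.25", "α = 0.05, power = 0.80" and "correlation among repeated measures r = 0.50". From these it concludes that "the minimum required sample is N = 159". The next sentence adds the attrition margin: "Allowing for 15% attrition, we plan to recruit N = 180", with about 60 in each diagnostic group.

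Section 2.14 says that recruitment continues "until the planned sample size (N = 180) is reached", and that enrolment closes at that number or at the end of the recruitment window if that comes sooner. So 180 is a ceiling. The article gives no other attrition rate and no target for the number of completers.

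**The concern.** An attrition allowance is meant to leave the required number in place after the expected losses. Here the required number, the expected loss and the recruitment target stand in adjacent sentences, and the third does not follow from the first two. If attrition is what the plan predicts, the study ends below the minimum that the plan sets for itself. Over-recruitment cannot make up the gap, because section 2.14 closes enrolment at 180.

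What is at stake is mainly the plan's internal consistency. Section 2.3 uses 180 to claim adequate precision for the primary and secondary analyses, but on the plan's own assumption about 153 patients will have complete follow-up.

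**Working it through.** **Inputs, all from section 2.3:** stated minimum 159; attrition 15%; recruitment target 180; f = 0.25; m = 4 timepoints; r = 0.50; α = 0.05; power 0.80.

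**Step 1. Can the target of 180 be reproduced?**

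| Calculation | Result |
|---|---|
| Correct inflation, N/(1 − d) = 159/0.85 | 187.06, so 188 |
| Common shortcut, N × (1 + d) = 159 × 1.15 | 182.85, so 183 |
| Completers from 180, 180 × 0.85 | 153 |
| Shortfall, 159 − 153 | 6 |
| Largest loss that 180 absorbs, 1 − 159/180 | 11.7% |

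Neither formula gives 180. With 188 recruits, 188 × 0.85 = 159.8 are expected to remain. The target is 8 recruits short of 188.

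**Step 2. Does 159 follow from the stated inputs?** For a within-subject F test, the noncentrality is λ = f² × N × m × ε/(1 − r), on (m − 1)ε and (N − 1)(m − 1)ε degrees of freedom.

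- N = 24, ε = 1: λ = 0.0625 × 24 × 4/0.5 = 12 on 3 and 69 df, power 0.817. This is the smallest N that reaches 0.80.
- N = 50, ε = 1/3 (the lower bound with four timepoints): λ = 0.0625 × 50 × 4/(0.5 × 3) = 8.33 on 1 and 49 df, power 0.808.

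So the stated inputs give 24, or 50 in the worst case, and not 159. Other readings do not give it either. A repeated-measures comparison between three groups needs 102, and the group-by-time interaction needs 30. Two effect-size definitions that leave r out need 61 and 176.

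One calculation does return exactly 159: a one-way between-groups ANOVA with three groups and f = 0.25, where λ = 0.0625 × 159 = 9.94 on 2 and 156 df and power is 0.805. The article names no such test, so this match is only an inference about how 159 arose.

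**Step 3. What does the shortfall cost?**

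| Test | Power at 159 | Power at 153 |
|---|---|---|
| Named within-subject test, ε = 1 | >0.999 | >0.999 |
| Named within-subject test, ε = 1/3 | 0.9992 | 0.9989 |
| Paired change with d = 0.5, α = 0.05/6 (Bonferroni over six pairwise contrasts) | 0.9998 | 0.9997 |
| Three-group one-way ANOVA (not named in the plan) | 0.805 | 0.788 |

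**Step 4. Precision at 153.** With r = 0.50 and equal SDs over time, the SD of a change score is SD × √(2 × (1 − 0.50)) = SD. The approximate 95% half-width for a mean change is 1.96/√153 = 0.158 SD, against 1.96/√159 = 0.155 SD at the stated minimum. For one diagnosis, 60 × 0.85 = 51 completers give 1.96/√51 = 0.274 SD.

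**The case against.** The strongest reply is that nothing follows from the error. Section 2.8 makes the within-subject repeated-measures ANOVA the primary analysis, and section 2.3 says that this is the test that was powered. On the stated inputs, 153 patients are several times the number needed. That stands, and it is why the point is minor.

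A second reply is that the mismatch depends on 159. Once the base figure is corrected, 180 covers 15% attrition many times over and the contradiction disappears. That also stands, and it is a reason to correct both figures together. It does not make the present sentence true: while 159 is the stated minimum, 180 with 15% loss falls below it.

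A third reply is that section 2.8 plans multiple imputation if data are missing at random, so patients lost after baseline may still contribute. This weakens the practical consequence. But section 2.3 does not offer imputation as a reason for a smaller margin, and it does not change what 15% of 180 is.

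A reader might go further and infer that the study is underpowered, that it must recruit 188, or that its power falls to 0.788. The documents do not support this. The 0.788 belongs to a three-group comparison that the article never names. Even there the change from 0.805 is 1.7 percentage points.

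**Conclusion.** The sentence is wrong as written, and the error is minor. On the plan's own figures, 180 recruits with 15% attrition give 153 completers, 6 below 159. Keeping 159 would need 188 recruits, and 180 tolerates only 11.7% loss. Nothing elsewhere in the article repairs this.

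The consequence for the primary analysis is negligible. Power for the named test at 153 is above 0.99 even at ε = 1/3, and the half-width of the interval for a mean change grows only from 0.155 to 0.158 SD. No extra patients are needed.

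This conclusion assumes that f = 0.25 is defined so that r enters the calculation, as the listing of r among the inputs implies. Under the least favourable definition that ignores r (λ = f² × N, requirement 176), power at 153 would be 0.736. That definition does not reproduce 159 and gives the stated r no role. The paired calculation from the article's own d ≈ 0.5 does not depend on this choice if d is read as the mean change divided by the SD of the change, and it gives 0.9997 at 153. The figure of 51 per diagnosis assumes 60 recruited in each group and equal loss across groups.

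**What to change.** Edit section 2.3 and leave the recruitment target and the 15% allowance as they are.

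1. Replace the attrition sentence with one such as: *N = 180 with 15% attrition gives about 153 completers (about 51 per diagnosis).*
2. Quote power and precision for the within-subject repeated-measures test at 153: power above 0.99, and a half-width of about 0.158 SD for a mean change overall and 0.274 SD within one diagnosis, under the assumptions above.
3. In the same edit, correct the 159. The stated inputs give N = 24, or 50 at ε = 1/3. If 159 came from a different calculation, name that test and its inputs.

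Restating the allowance as 11.7% is not recommended. It would make the arithmetic agree only by fitting the attrition assumption to the chosen number, and it would keep 159 as the minimum.

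The cost is a few sentences in section 2.3. Section 2.14 needs no change, because N = 180 stays, and neither recruitment nor the analysis changes.

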### 2.4. Training and Intervention Fidelity

All nurse interventors will complete a standardized 4 h training covering the following: (i) theory-driven education anchored to SC-CII domains; (ii) motivational interviewing techniques; (iii) telecommunication standards and privacy; (iv) digital health literacy coaching; and (v) documentation on the electronic case report form (eCRF). To ensure fidelity, a random 10% of tele-education sessions will be audited by a clinical supervisor using a structured checklist (adherence to content, dose, pacing, patient engagement, and shared goal setting). Deviations will prompt feedback and corrective training.

To ensure theoretical coherence and transparency, the intervention content was mapped to the Behaviour Change Techniques Taxonomy version 1 (BCTTv1) developed by Michie et al. [22]. Each educational session incorporates specific BCTs aligned with the self-efficacy and health belief frameworks, including “goal setting (behavior),” “self-monitoring of behavior,” “feedback on performance,” “problem solving,” “information about health consequences,” and “action planning.” This mapping allows for structured replication, facilitates fidelity assessment, and provides a framework for analyzing which components most effectively promote self-care maintenance, monitoring, and management behaviors.

### 2.5. Intervention

The PROSELF intervention is a nurse-led, theory-based digital program delivered via encrypted video calls and supported by asynchronous materials (brief videos, PDFs, checklists, reminders). Each session lasts 30–40 min and is individualized through shared agenda setting and goal planning. Content maps directly onto maintenance, monitoring, and management, integrating Bandura’s Self-Efficacy (mastery, vicarious experiences, persuasion, and emotional regulation) and Health Belief Model constructs (perceived risk, benefits, barriers, and cues to action).

Session 1: (T0, baseline; focus: maintenance). Disease education; medication routines; nutrition and physical activity; identification of personal goals; and barrier mapping with concrete strategies.Session 2: (T1, 3 months; focus: monitoring). Symptom perception and interpretation; home tracking (glycemia, SpO_2_, peak flow, and blood pressure as relevant); warning signs and thresholds; digital logs; and feedback on data quality.Session 3: (T2, 6 months; focus: management). Action plans for symptom exacerbations; problem solving; when/how to contact providers; aligning self-management actions with care plans; and relapse prevention.Session 4: (T3, 12 months; focus: reinforcement and consolidation). Review of progress; consolidation of habits; prevention of regression; update of personal action plans; and refreshing digital literacy.

All sessions are delivered on a GDPR-compliant platform with appointment reminders and secure authentication. Between visits, patients receive brief cues to action (SMS/email reminders) and links to concise educational resources aligned with international clinical guidance (e.g., GOLD for COPD; ADA standards for diabetes; and ESC guidance for CVD) to reinforce self-efficacy and adherence to the agreed goals.

Each session was systematically aligned with the Behaviour Change Technique Taxonomy (BCTTv1) to operationalize the theoretical constructs derived from Bandura’s Self-Efficacy Theory and the Health Belief Model. Specifically, the intervention includes techniques such as information about health consequences, goal setting (behavior), action planning, self-monitoring of behavior, feedback on performance, and problem solving, which correspond to motivational and cognitive determinants of self-care behaviors. Mapping BCTs to each theoretical construct supports transparency, replicability, and evaluation of which techniques are most effective in promoting sustained self-care across conditions.

### 2.6. Instruments and Data Collection

We use validated instruments to capture global and disease-specific self-care, HRQoL, and social support. Administration occurs at T0, T1, T2, and T3 through encrypted forms; the platform enforces completeness checks, range validations, and time stamps. Nurse assistance is available for technical or comprehension issues.

**Self-Care of Chronic Illness Inventory (SC-CII)**. The SC-CII operationalizes Riegel’s theory across maintenance, monitoring, management (and confidence when applicable) as a trans-diagnostic measure [23]. Items are Likert-type; domain and total scores are standardized to 0–100 (higher = better self-care). The primary endpoint is the T0 → T3 change in total score, with domain-level analyses a priori. An increase of ≥8 points is considered clinically meaningful, consistent with the validation literature. Psychometrics across languages and Italian samples are robust (Cronbach’s α usually ≥0.80, test–retest ICC ≥ 0.75).

**Self-Care of Heart Failure Index (SCHFI, v7.x)**. Disease-specific self-care in HF, providing maintenance, management, and confidence scores, is standardized to 0–100 [24]. Psychometric testing has shown good reliability (Cronbach’s α = 0.76–0.90 across domains) and construct validity in multiple international validations, including the Italian version. Test–retest reliability was satisfactory (ICC > 0.70). While thresholds vary by study, values ≥ 70 are often interpreted as adequate self-care.

**Self-Care of Diabetes Inventory (SCODI)**. Targets T2DM self-care behaviors spanning adherence, lifestyle, and glucose self-monitoring, aligned with Riegel’s domains [25]. Scores are transformed to 0–100. The instrument demonstrates good internal consistency (Cronbach’s α = 0.80–0.88) and factorial validity in the Italian population, with acceptable test–retest reliability (ICC > 0.75).

**Self-Care of COPD Inventory (SCCOPD)**. Measures BPCO self-care (maintenance/monitoring/management), including medication routines, symptom recognition, and timely action [26]. Scores are transformed to 0–100. The SCCOPD has shown strong psychometric properties with Cronbach’s α = 0.83–0.89 and adequate construct validity in both English and Italian validations.

**EQ-5D-5L**. A generic HRQoL measure across five dimensions with five severity levels, plus a 0–100 VAS [27]. The EQ-5D-5L demonstrates high test–retest reliability (ICC ≥ 0.80) and convergent validity with SF-36 physical and mental summary scores. The validated Italian version has shown comparable psychometric performance. Administration: 2–3 min.

**SF-36**. A multidimensional HRQoL profile with eight domains and Physical/Mental Component Summary (PCS/MCS) using norm-based scoring (mean 50, SD 10) [28]. Psychometric analyses have shown high internal consistency (Cronbach’s α typically >0.85 for all subscales) and strong test–retest reliability (ICC ≥ 0.80) in both general and chronic populations.

**Multidimensional Scale of Perceived Social Support (MSPSS)**. Assesses perceived social support from family, friends, and significant others (12 items; 1–7 Likert), providing domain and total means (higher = more support) [29]. The MSPSS demonstrates excellent reliability (Cronbach’s α = 0.88–0.94) and factorial stability across languages, including the Italian adaptation.

**Data capture, scoring, and quality controls**. The eCRF performs automated scoring (including 0–100 transformations), flags outliers (e.g., straight-lining, extreme completion times), and generates consistency reports. An audit trail logs user ID, date/time, and rationale for any data edits.

**Missing data (instrument-specific)**. We follow the instrument manuals. Where permitted, if ≤20% of the items in a subscale are missing, we apply person-mean imputation within that subscale; otherwise, the subscale is marked as missing and handled at the analysis level. We will document domain-specific missingness in the Results section of the full study report and address it using dataset-level multiple imputation, as described in the Section 2.8.

**Language versions and permissions**. We employ validated Italian versions where available. EQ-5D-5L is used under EuroQol terms; SF-36 will follow the owner’s license (or the RAND equivalent, if adopted) and will be explicitly stated in the submission; MSPSS is used with proper citation. All permissions will be secured before data collection and summarized in Ethics and Permissions.

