### 2.2. Setting and Participants

The study will be conducted in community and primary-care services across Southern Italy, including FCN clinics, general practice networks, and chronic disease outpatient pathways. Inclusion: adults (≥18 years) with a confirmed diagnosis of COPD, T2DM, or CVD; clinically stable at enrollment; access to internet-enabled devices; ability to consent and participate in tele-education. Exclusion: cognitive or psychiatric conditions precluding participation—such as moderate to severe dementia, major depressive disorder with psychotic features, schizophrenia spectrum disorders, or acute manic or psychotic episodes—severe uncorrected sensory impairments, or concurrent enrollment in interventional trials. Participants will be referred by FCNs and General Practitioners (GPs) during routine care or teleconsultation. Additionally, participants who already demonstrate optimal or near-optimal self-care behaviors—such as consistent treatment adherence, regular symptom monitoring, and proactive disease management—will be excluded based on baseline screening, to ensure measurable intervention effects. Eligibility will be verified using data from participants’ electronic medical records, reviewed and confirmed by the referring Family and Community Nurses (FCNs) or General Practitioners (GPs). Only objectively documented diagnoses (COPD, T2DM, or CVD) and clinical stability will be considered valid for inclusion. Self-reported data will be limited to sociodemographic and behavioral variables such as education, smoking habits, and physical activity.

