### 2.7. Outcomes

**Primary outcome**. Change in SC-CII total (0–100) from T0 to T3 (12 months), with domain-specific analyses (maintenance, monitoring, and management). An ≥8-point increase is treated as clinically important.

**Secondary outcomes**. Change in disease-specific self-care (SCHFI/SCODI/SCCOPD), HRQoL (EQ-5D-5L index and VAS; SF-36 PCS/MCS), perceived social support (MSPSS), and engagement/satisfaction with the digital education (brief evaluation form anchored to established telehealth assessment domains).

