### 2.8. Statistical Analysis

Analyses will be conducted in R studios version 4.4.0. (R Foundation for Statistical Computing, Vienna, Austria; https://www.r-project.org). We will summarize baseline characteristics using means (SD) or medians (IQR) and frequencies (%). Normality will be assessed with Shapiro–Wilk tests and Q–Q plots.

**Primary analysis**. Within-subject change over time will be evaluated using repeated-measures ANOVA (or Friedman for non-normal data) on SC-CII total and domains. When the omnibus test is significant, we will perform timepoint contrasts with Bonferroni-adjusted *p*-values. We will report mean differences with 95% confidence intervals and effect sizes (partial η^2^ and Cohen’s d for pairwise changes) [30].

**Secondary analyses**. Analogous repeated-measures models will be applied to disease-specific self-care, EQ-5D-5L, SF-36 (PCS/MCS), and MSPSS. Subgroup analyses will examine differences by diagnosis (COPD vs. T2DM vs. CVD) and baseline digital literacy strata (derived from a short digital-skills screener). Multivariate linear regression will explore predictors of 12-month improvement (ΔSC-CII total), including age, sex, education, diagnosis, baseline score, and digital engagement metrics (attendance, completion time, and message interactions). Collinearity will be checked via the variance inflation factors.

**Missing data**. We will evaluate missingness patterns with Little’s MCAR test. If data are missing at random, we will apply multiple imputation (m = 5–10 datasets), including all variables used in the analysis models. Sensitivity analyses will compare imputed vs. complete-case results to assess robustness.

**Reliability**. Internal consistency will be assessed at each timepoint using Cronbach’s α, with α ≥ 0.70 considered acceptable [31].

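### Any cardiovascular disease is eligible, but the only cardiovascular self-care scale is a heart-failure scale, and the plan has no rule for CVD patients without heart failure

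*Protocol article*

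**What the plan says.** **Who is enrolled.** Section 2.2 includes "adults (≥18 years) with a confirmed diagnosis of COPD, T2DM, or CVD; clinically stable at enrollment". On verification it adds: "Only objectively documented diagnoses (COPD, T2DM, or CVD) and clinical stability will be considered valid for inclusion". Neither the inclusion nor the exclusion criteria narrow CVD to heart failure. Section 2.5 likewise ties the cardiovascular education material to ESC guidance for CVD in general.

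**Which scales are used.** Section 2.6 names three disease-specific instruments: the SCODI for type 2 diabetes, the SCCOPD for COPD, and the SCHFI, described as "Disease-specific self-care in HF, providing maintenance, management, and confidence scores". No other cardiovascular instrument is named. The SC-CII, which carries the primary endpoint, is described as trans-diagnostic.

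**How they are used.** Section 2.7 lists as a secondary outcome "Change in disease-specific self-care (SCHFI/SCODI/SCCOPD"). Section 2.14 states: "Each assessment includes completion of the SC-CII and disease-specific self-care scales (SCHFI/SCODI/SCCOPD"). Table 2 shows a disease-specific scale at T0 and T1 and all instruments at T2 and T3. Section 2.8 says: "Analogous repeated-measures models will be applied to disease-specific self-care, EQ-5D-5L, SF-36 (PCS/MCS), and MSPSS". No HF subset is mentioned in any of these places.

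**What happens to missing scores.** Section 2.6 fills in a subscale by the person mean when up to 20% of its items are missing. Beyond that the subscale is set to missing and passed to the multiple imputation of Section 2.8, which applies if data are judged missing at random.

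**The concern.** The eligible population is wider than the population for which the cardiovascular instrument is described. The psychometric support that Section 2.6 gives for the SCHFI is for a heart-failure scale, and nothing in the article supports its use in, for example, stable coronary disease or hypertension without HF. Yet the schedule is written as if every participant had a matching disease-specific scale.

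The CVD arm of a named secondary outcome is at stake. If patients without HF answer the SCHFI, their change scores have no stated meaning but enter the same repeated-measures model as those of patients with HF. If they do not answer it, the missing-data rules could create HF self-care scores for people who do not have HF. Either way, the reported change would not describe a definable group of patients.

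**Working it through.** The plan states no figure to reproduce on this point. The check compares the sections and then illustrates the size.

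**Step 1: match diagnoses to scales.**

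| Eligible diagnosis (2.2) | Scale in 2.6 | Scope given in 2.6 | Match |
|---|---|---|---|
| T2DM | SCODI | T2DM self-care | yes |
| COPD | SCCOPD | COPD self-care | yes |
| CVD, any | SCHFI | self-care in HF | only for the HF part |

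The article never writes that the CVD group receives the SCHFI. That link follows by elimination from three diagnoses and three scales.

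**Step 2: take both possible readings for a CVD patient without HF.**

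- *The patient completes the SCHFI.* This satisfies 2.14 and Table 2, but applies the scale outside the scope given in 2.6. The completeness checks that the platform enforces (2.6) would encourage answers to every item presented.
- *The patient does not complete the SCHFI.* This respects the scope in 2.6, but no disease-specific scale is left for the patient, contrary to 2.14 and Table 2. The score is then blank in a dataset for which 2.8 plans multiple imputation of all analysis variables. Such a value is undefined rather than unobserved, so a missing-at-random argument does not apply to it. Comparing imputed with complete-case results (2.8) does not say which patients should count.

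Neither reading fits all of the stated text.

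**Step 3: number of patients for whom the scale applies.** Inputs: "we plan to recruit N = 180 (≈60 per diagnostic group") and 15% attrition, both from Section 2.3. The HF share p among CVD patients is not given; 20% to 60% is an assumption used only for illustration.

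- CVD completers: 60 × (1 − 0.15) = 51.
- With HF at p = 0.20: 51 × 0.20 = 10.2, about 10; without HF about 41.
- With HF at p = 0.60: 51 × 0.60 = 30.6, about 31; without HF about 20.

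**Step 4: effect on precision.** With the same standard deviation, the confidence interval for a mean change widens by 1/√p relative to all 51 completers: 1/√0.20 = 2.24 and 1/√0.60 = 1.29.

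**Step 5: effect on power, using the design values of Section 2.3** (f = 0.25, four timepoints, r = 0.50, α = 0.05; sphericity assumed). The noncentrality is λ = f² × n × m / (1 − r) = 0.0625 × n × 4 / 0.5 = 0.5n, with 3 and 3(n − 1) degrees of freedom.

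| Assumed HF share | HF patients of 60 | Completers n | λ | Power |
|---|---|---|---|---|
| 100% | 60 | 51 | 25.5 | 0.99 |
| 50% | 30 | 26 | 13.0 | 0.85 |
| 25% | 15 | 13 | 6.5 | 0.51 |

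**The case against.** The strongest reply is that the text allows a harmless reading. The SCHFI is labelled for HF, Section 2.6 promises to follow the instrument manuals, and Table 2 speaks only of a disease-specific scale without assigning one to each group. The study team may intend the SCHFI for HF patients alone, and a condensed article may leave an eCRF branching rule to the full protocol. This stands in part: that every CVD patient would be given the SCHFI is an inference, not a statement of the plan. It does not remove the problem. Eligibility, instrument scope and schedule are all stated, and they cannot all hold for a CVD patient without HF.

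A reader might infer more than the documents support:

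- *That the three scales will be pooled or compared across diagnoses, where the lack of a monitoring score on the SCHFI would matter.* No section plans pooling. Section 2.8 speaks of models in the plural, and its subgroup sentence names no outcome.
- *That the plan counts on all 60 CVD patients for the SCHFI.* Section 2.3 gives the group size and says nothing about SCHFI denominators.
- *That the CVD result is uninterpretable.* Diagnoses are confirmed from medical records (2.2), so an HF-only analysis remains possible if HF is recorded in the study data.
- *That many subscales will be lost to the 20% rule.* The completeness checks make blank items less likely, and the item wording is not shown.

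**Conclusion.** The point holds as a mismatch between population and instrument. The article enrols any CVD, offers only an HF scale for that group, schedules a disease-specific scale at every assessment, and does not say what applies to CVD patients without HF.

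It is confined to one secondary outcome in one of three diagnostic groups. The primary SC-CII analysis and the SCODI and SCCOPD outcomes are untouched. The size depends on the HF share, which the article does not give: the figures of about 10 to 31 patients with HF and 20 to 41 without, out of 51 completers, rest on the assumed 20% to 60%. If all recruited CVD patients had HF, the problem would disappear, but nothing in Section 2.2 ensures that. It should be corrected before recruitment and does not threaten the main result.

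**What to change.** In Sections 2.6, 2.7 and 2.14 and in Table 2, state that:

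- the SCHFI is administered and analysed only in CVD patients with heart failure documented in the medical record;
- other CVD patients have the SC-CII as their self-care measure;
- SCHFI scores are not imputed for patients without HF (with a matching sentence in the missing-data paragraph of Section 2.8);
- the SCHFI result is reported as an HF-subset result, with its expected n given in advance.

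This needs wording, a field recording HF at baseline and one branching rule in the eCRF. It changes neither eligibility nor the set of instruments. Ethics approval is pending and recruitment has not begun (2.11), and registration is still to come (2.13), so the change can be made before any baseline is collected.

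The downside is that fewer CVD patients will have a disease-specific score, so this secondary outcome will be less precise: at the assumed HF shares, its confidence interval would be about 1.3 to 2.2 times as wide as with all 51 completers.
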